### Outcome measurement

2.6

#### Motor-evoked potential

2.6.1

In this study, MEP will be induced by the application of TMS over the M1 after positioning the center of the coil at 45° lateral to the sagittal midline (Muellbacher et al., 2000). An optimal TMS position is chosen to record the maximum potential amplitude of the abductor pollicis brevis (APB), identified as the hotspot area, which will be called conventional hotspot area for this trial (Muellbacher et al., 2000). The stimulation intensity of the M1 is determined by motor threshold, which is the intensity at which the first potential or muscle contraction occurs, starting at 40% of the maximum intensity of the stimulator and is increased by 5%.

The MEP amplitude and latency will be assessed. Latency is defined as the period from the start of a single-pulse TMS to the emergence of a wave peak in milliseconds, whereas amplitude is the distance from the baseline to the wave peak in microvolts (Lee et al., 2015).

The MEP is assessed immediately before and after each tDCS session. Hence, each group will be assessed six times over the course of the trial by investigators who are blinded to the group allocation.

#### Primary outcome

2.6.2

The difference between groups in MEP amplitude recorded before and after each tDCS session (optimized-active, conventional-active and sham tDCS) over the M1 hand-knob area selected by the investigator on the 3D brain model of the tES LAB.

#### Secondary outcomes

2.6.3

The difference between groups in the MEP amplitude over the conventional hotspot recorded before and after each tDCS session (optimized-active, conventional-active and sham tDCS).The MEP latency changes between groups recorded before and after each tDCS session (optimized-active, conventional-active and sham tDCS) over the conventional hotspot area and the M1 hand-knob area selected by the investigator on the 3D brain model of the tES LAB.Correlation between MEP changes before and after each tDCS session (optimized-active, conventional-active and sham tDCS) over the conventional hotspot area and the M1 hand-knob area selected by the investigator on the 3D brain model of the tES LAB, and the E-field generated at the structural M1 hand-knob.

### Statistical analyses

2.7

The results of the outcome assessment analysis will be presented as mean, standard deviation (SD), standard error (SE), and confidence interval, with the statistical significance threshold set at *p* < 0.05. The Shapiro–Wilk test will be employed to assess the normality of the data. If normality is met, a repeated measures ANOVA test will be used for within-and in-between groups analysis, and Tukey’s test will be used for *post hoc* analyses. If normality is not met, the Friedman test will be used with the Wilcoxon rank-sum test to compare independent variables. Additionally, the correlation between the pre-post MEP conventional hotspot and the M1 hand-knob area selected by the investigator on the 3D brain model of the tES LAB with the E-field generated at the structural M1 hand-knob area will be analyzed.

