### Trial design

2.1

The present study protocol is a prospective single-center crossover randomized control trial designed to determine the effect of personalized tDCS electrode positioning on the activation of the cortical region responsible for finger movement in patients with stroke. The crossover design will be divided into six groups (four groups of eight participants each and two groups of nine participants each). All participants will randomly receive one session of conventional-active, optimized-active, or sham tDCS. After a 24-h washout period, the groups will cross to receive a different tDCS intervention until each group receives all three alternatives. Figure 1 provides a detailed explanation of this procedure and Table 1 displays the activities to be completed at each visit during the trial.

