#### Randomization

2.3.4

Participants who meet the inclusion and none of the exclusion criteria will be randomly assigned to one of six groups. A 1:1 random ratio is used to locate the participants in each group (Figure 1). Due to the required sample size for this study, some groups will have an unequal number of participants. An independent statistician will issue randomization numbers.

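### The primary comparison is worded as a between-groups analysis, although the six randomised groups are treatment orders and every treatment contrast lies within participants

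*Protocol article*

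**What the plan says.** Section 2.3.4 states that participants "will be randomly assigned to one of six groups". Section 2.1 gives the sizes as "four groups of eight participants each and two groups of nine participants each" and says that "the groups will cross to receive a different tDCS intervention until each group receives all three alternatives". With three treatments over three treatment visits (V2, V3 and V4 in Table 1), six groups are the six possible orders. MEP is recorded before and after each session, so "each group will be assessed six times over the course of the trial" (section 2.6.1).

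Section 2.6.2 nevertheless opens the primary outcome with "The difference between groups in MEP amplitude recorded before and after each tDCS session" and then lists the three session types. Section 2.7 says that, if normality holds, "a repeated measures ANOVA test will be used for within-and in-between groups analysis". Otherwise it names the Friedman test together with the Wilcoxon rank-sum test. Section 2.3.3 sizes the trial on the within-between interaction of a repeated-measures ANOVA.

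**The concern.** The word groups carries two meanings. In sections 2.1 and 2.3.4 it means the randomised orders. In section 2.6.2 it is attached to the session types. The hypothesis in the Discussion compares sessions, and since each person has all three, that comparison is made inside each person. A between-groups term does not estimate it.

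Two other statements lean the same way: the within-between interaction used for sizing, and a rank-sum test, which is for independent samples, placed after Friedman, which is for related samples. At stake is whether the named primary test isolates the effect of electrode position, and how much power it has to do so.

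**Working it through.** **1. The plan's own figure.** Inputs from section 2.3.3: f = 0.2193764, alpha 0.05, power 0.95, N = 45. Number of groups k, measurements m and correlation ρ are not stated. For the interaction, λ = f²·N·m/(1−ρ), df1 = (k−1)(m−1), df2 = (N−k)(m−1).

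With k = 3, m = 6 and ρ = 0.5 (assumed): λ = 0.048126 × 45 × 6 / 0.5 = 25.99, df = 10 and 210, power 0.9545. At N = 44 power is 0.9493, so 45 is reproduced. Then 45/0.90 = 50. At ρ = 0.5 the other eight combinations of k and m from 2, 3 and 6 need between 36 and 109. The match fits three treatments handled as three groups measured six times. It is not proof: k = 6, m = 6 with ρ about 0.64 also reaches 45.

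**2. Groups as orders, between-group term.** A participant's mean over the three sessions contains (τ_opt + τ_conv + τ_sham)/3 plus the mean of the three visit effects. Both are the same in every order, so treatment cancels. In simulation (20,000 runs, orders 8/8/8/8/9/9) this term rejected about 5% of the time, with or without a treatment effect of 0.5 within-participant SD.

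**3. Groups as orders, interaction term.**
- Order by visit does contain treatment, but spreads it over 10 degrees of freedom: power 41%, against 72% for the within-participant treatment test adjusted for period.
- Order by treatment contains the visit effect. With no treatment effect it rejected 12, 44 and 93% of the time for total linear shifts from V2 to V4 of 0.3, 0.6 and 1.0 SD.

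**4. Groups as sessions, between factor.** The error becomes the total variance, σ_w²/(1−ρ), where ρ is the correlation between sessions of one person. For assumed ρ = 0.3, 0.5 and 0.7 the factor is 1/0.7 = 1.43, 1/0.5 = 2.00 and 1/0.3 = 3.33.

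**5. Session within participant, one-way, no period term.** A linear slope s per visit has centred values −s, 0, s, with sum of squares 2s² per person on about 2 degrees of freedom. It therefore adds about s² to the error variance: 0.3² = 0.09, 0.5² = 0.25, 0.8² = 0.64. The exact factor of 50/49 gives 9.2, 25.5 and 65.3%. Type I error falls to about 1 to 4%. For a 0.5 SD effect, power drops from about 72% to 71, 65 and 51%. It varies by several points with which two orders hold nine participants: another placement gave 64% at slope 0.3 and 54% at slope 0.5.

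**6. Sequence by session, session effect within participant.** The sequence-by-session interaction absorbs the visit effect: error variance 1.00, type I error about 5%, power about 72% at every slope.

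**7. Bias.** The two extra participants can unbalance the mean visit of two treatments by at most (2 + 1)/50 = 0.06 visit. At slopes of 0.3, 0.5 and 0.8 SD that is 0.018, 0.030 and 0.048 SD.

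**The case against.** The strongest reply is that section 2.7 does name a repeated-measures ANOVA, in which session would normally be a within-participant factor, and that Friedman is its related-samples counterpart. Read as sequence (between) by session (within), the sentence gives a valid treatment test and removes period without naming it. That stands, and it limits the point: the power loss depends on the reading.

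It also stands that period terms and missing-data rules are commonly left to a statistical analysis plan, so the missing period term alone would be no finding. Further, a visit shift that moves the pre- and post-session MEP equally cancels in the change. Only a visit effect on the change itself matters, and the document gives no figure for one.

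What does not fall away is the stated structure. The primary outcome is worded as a between-group difference, the sizing uses a within-between interaction, and the fallback includes an independent-samples test. An analyst following the text could choose any of the models in steps 2 to 6, and they answer different questions.

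**Conclusion.** The point holds as a misfit between the stated analysis structure and the crossover; it should be corrected. Under two readings the between-group term is the wrong test. Under the one-way reading the test is valid but conservative, with error variance up by about 9, 25 or 64% at the assumed slopes. Under the sequence-by-session reading nothing is lost. Slopes, ρ and the 0.5 SD effect are assumptions.

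Stronger inferences are tempting but not supported:
- That visit effects seriously bias the contrast: with the planned order sizes the shift is at most about 0.05 SD.
- That participants who miss a session will be deleted: no such rule is stated, and section 2.3.3 allows for 10% dropout.
- That a parallel-group analysis is intended: the three-by-six layout is inferred from a match at one assumed ρ.
- That 50 is too few: a period-adjusted within-participant test with the same f needs 109, 77, 56 or 34 evaluable participants at ρ = 0, 0.3, 0.5 or 0.7, and carrying f over is itself an assumption.

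**What to change.** In sections 2.6.2 and 2.7, state the primary comparison as between session types within participants, and reserve one term, such as sequence, for the six randomised orders.

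Name the primary analysis as a linear mixed model on session-level data. The outcome is the pre-to-post change in MEP amplitude at the hand-knob, or post-session MEP with pre-session MEP as covariate, chosen in advance. Fixed effects are session type, period (V2, V3, V4) and sequence, with participant as random effect, and all completed sessions are used. Report optimized minus conventional and optimized minus sham with 95% confidence intervals. Any rank-based pairwise fallback should likewise be a paired test, such as the signed-rank test.

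As a separate check of the washout, outside this model because the outcome differs, compare pre-session MEP at V3 and V4 by the preceding session type.

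The cost is analysis wording and a few degrees of freedom: two for period, which takes the session-test error from 98 to 96 with 50 complete participants, and five for sequence, from the between-participant part. Section 2.9 reports recruitment as ongoing, so the change can be fixed before analysis.

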**Discussion:**

We hypothesize that the optimized-active tDCS session would show a greater increase in MEP amplitude over the target area in patients with subacute and chronic stroke than conventional and sham tDCS sessions.

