Although the use of computational modeling in research and clinical practice has been recommended, its use has been scarce because it requires numerous software packages and professionals to create 3D head models and perform E-field calculations, which consumes time and resources (Yoo et al., 2022; Lee et al., 2023). Furthermore, accurate creation of a 3D head model is crucial for calculating tDCS-influenced E-field, especially as the segmentation of stroke-affected tissue directly affects the strength and orientation of the E-field in the target area (Lee et al., 2023). Recently, software capable of constructing a 3D realistic head model and accurately calculating the tDCS-induced E-field in patients with stroke in a relatively short period of time has been developed. This software allows the user to determine the optimal electrode position for each individual according to brain structure, stroke lesion, electrical conductivity, and electrode properties (Yoon et al., 2023).

Therefore,, the aim of the present crossover randomized control trial is to determine the immediate effect of personalized tDCS electrode positioning on the activation of the cortical region responsible for finger movement in patients with sub-acute or chronic stroke using MEP. Our hypothesis is that compared to conventional and sham stimulation, personalized electrode positioning will show changes in MEP amplitude over the cortical region responsible for finger movement in this population. Furthermore, we hypothesize that the participants would tolerate the tDCS sessions without experiencing any significant adverse events. We aim to reduce the inconsistencies in tDCS intervention in patients with stroke and to improve motor function in these patients, especially in the upper extremity.

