However, this study presents some limitations. First, only the immediate effects of tDCS will be evaluated as the participants will be assessed immediately after the application. Therefore, the short-and long-term effects of tDCS should be investigated in future studies. Second, the study will include and analyze data combined from patients with sub-acute or chronic stroke, which should be interpreted independently in future research to determine the effect of optimized tDCS electrode locations according to each stroke phase. Furthermore, inclusion of patients with acute stroke is necessary. Third, the study sample includes participants within a wide age range (young and older adults), which may influence the results.

As expressed before, we hypothesize that the optimized active tDCS session will show a greater increase in MEP over the cortical region responsible for finger movement in patients with sub-acute or chronic stroke than conventional and sham tDCS sessions. Additionally, we hypothesized that participants would tolerate the tDCS sessions without any significant adverse events.

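### The hypothesis is optimized over both conventional and sham, but section 2.7 plans ANOVA with all-pairs Tukey and does not tie the conclusion to those two contrasts: valid, but conservative and poorly aligned

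*Protocol article*

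**What the plan says.** The directed hypothesis appears twice. The Abstract expects optimized-active tDCS to show a "greater increase in MEP amplitude over the target area in patients with subacute and chronic stroke than conventional and sham tDCS sessions". Section 3 (Discussion) repeats it: "we hypothesize that the optimized active tDCS session will show a greater increase in MEP" at the finger area, "than conventional and sham tDCS sessions". The end of section 1 is looser and gives no direction: "compared to conventional and sham stimulation, personalized electrode positioning will show changes in MEP amplitude".

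Section 2.6.2 defines the primary outcome without direction, across all three sessions: "The difference between groups in MEP amplitude recorded before and after each tDCS session (optimized-active, conventional-active and sham tDCS", measured at the M1 hand-knob.

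Section 2.7 sets the threshold at p < 0.05. For normal data, "a repeated measures ANOVA test will be used for within-and in-between groups analysis", and "Tukey’s test will be used for *post hoc* analyses". Otherwise, "If normality is not met, the Friedman test will be used with the Wilcoxon rank-sum test to compare independent variables".

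Section 2.3.3 sizes the trial on a within-between interaction in a repeated measures ANOVA, with f = 0.2193764, 5% type I error and 95% power. This gives 45 participants, and 50 after 10% dropout. Neither named contrast is the basis of the sizing.

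**The concern.** The hypothesis consists of two within-patient comparisons, and the question about electrode optimization rests on one of them, optimized versus conventional. Section 2.7 plans an undirected test of any difference among three sessions, followed by a procedure that protects all three pairs. This has two consequences.

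- A significant ANOVA need not bear on optimization. It can arise because both active sessions exceed sham by the same amount.
- Tukey spends part of the error rate on conventional versus sham. If the claim needs both named contrasts to succeed, no multiplicity adjustment is required, and the Tukey penalty is power lost on the two comparisons that matter.

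At stake are power for the actual claim and a clear rule for when the data support it.

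**Working it through.** **1. The plan's own figure.** The noncentrality for the within-between interaction is λ = f²·N·m/(1 − ρ), with df (k − 1)(m − 1) and (N − k)(m − 1). The article gives f, N, alpha and power, but not k, m or ρ for this calculation. Assuming k = 3, m = 6 (section 2.6.1 has six assessments) and ρ = 0.5:

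- λ = 0.048126 × 45 × 6 / 0.5 = 25.99, with df 10 and 210
- power = 0.955 at N = 45, and 45/(1 − 0.10) = 50

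The figure reproduces. Other settings also give 45, for example k = 3, m = 2, ρ = 0.75. In every such setting the 95% is power for an omnibus F-test, not for a contrast.

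**2. Critical values.** With 45 completers and three sessions, the residual df is 2 × 44 = 88.

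- Tukey: studentized range 0.95 quantile (3 means, 88 df) divided by √2 = 2.384, or p = 0.019 per pair
- Unadjusted, pooled error: t(0.975; 88) = 1.987
- Unadjusted, contrast-specific variance: t(0.975; 44) = 2.015

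**3. Loss on one contrast.** If unadjusted power is p, the standardized effect is δ = 1.987 + z(p), and power under Tukey is Φ(δ − 2.384).

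| Unadjusted power | δ | δ − 2.384 | Power under Tukey | Extra participants to restore it |
|---|---|---|---|---|
| 80% | 2.829 | 0.445 | 67% | about 30% |
| 90% | 3.269 | 0.885 | 81% | about 26% |
| 95% | 3.632 | 1.248 | 89% | about 23% |

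Restoring the power would take about 55 to 59 completers in place of 45.

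**4. Power to win both contrasts.** Place the session means at s·(1, c, 0) for optimized, conventional and sham, with residual variance 1. An F-test on 2 and 88 df has 95% power at λ = 15.98, so s = √(15.98/(45·Σ)), where Σ is the sum of squared deviations of (1, c, 0) from its mean. The contrast noncentralities are (1 − c)·s·√(45/2) against conventional and s·√(45/2) against sham. Joint power is by simulation. The values of c are assumptions.

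| Conventional lies at | Σ | s | Noncentrality vs conventional / vs sham | Both, Tukey | Both, unadjusted 5% |
|---|---|---|---|---|---|
| sham (c = 0) | 0.667 | 0.730 | 3.46 / 3.46 | 77% | 88% |
| one third (c = 1/3) | 0.519 | 0.828 | 2.62 / 3.93 | 58% | 73% |
| midway (c = 1/2) | 0.500 | 0.843 | 2.00 / 4.00 | 35% | 50% |

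The unadjusted column uses pooled error. Contrast-specific variance (44 df) costs little: a single contrast at 80% becomes 79%.

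**5. ANOVA without optimization.** Set optimized equal to conventional, with both above sham, again at 95% omnibus power. In 94% of simulated trials the F-test is significant with no Tukey win for optimized over conventional.

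**6. Error rate of the two-contrast rule.** When optimized equals conventional and sham is far lower, requiring both contrasts at two-sided 5% in favour of optimized gives a false claim in 2.5% of trials.

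**7. Where the loss arises.** With conventional at sham, both-contrast power at unadjusted 5% is 87.8% without a prior significant F and 87.5% with it. The ANOVA step costs almost nothing; the loss comes from Tukey's third pair.

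**The case against.** The strongest reply is that nothing here is invalid. Tukey includes both contrasts of interest and is conservative, so Tukey wins on both would properly support the hypothesis. Protecting all three pairs is a conventional choice, and section 2.6.2 does span all three sessions. This stands, and it limits the point to alignment and efficiency.

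A reader might infer that the trial will be declared positive on the ANOVA alone. The article does not say so. It gives no success rule, and such a rule may sit in the full protocol or analysis plan. The 94% figure shows what an ANOVA result cannot establish, not what the sponsor intends to claim.

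The hypothesis could also be read as two claims, each open to separate success. Two unadjusted 5% tests would then not control the familywise error, and an adjustment would be needed. Even so, Dunnett's value for two comparisons (about 2.25) is below Tukey's 2.384.

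Two further inferences are tempting but unsupported:

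- **Tukey fails because the difference variances are unequal.** The article describes variable response between patients but gives no variances, so this is conjecture.
- **A single power figure follows from the plan's f.** With conventional midway and f applied to three session values, power for optimized versus conventional is 29% under Tukey and 43% unadjusted at correlation 0.5, but 57% and 71% at 0.75. The article states no correlation. Only the gap of about 14 points is stable.

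Finally, the Tukey penalty applies only if normality holds. The Friedman branch carries none, though it does not name the two contrasts either.

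**Conclusion.** The point holds as a matter of alignment and efficiency in the normal-data branch, and it is worth correcting. The planned ANOVA with Tukey is valid, but it is stricter than a both-contrasts claim needs and is not tied to that claim. The loss is 6 to 13 percentage points on a single contrast with 80 to 95% unadjusted power, and 11 to 15 points on winning both in the three scenarios shown. The 95% in section 2.3.3 should not be read as power for the hypothesis: under Tukey, power for both contrasts is 35 to 77% in those scenarios.

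These results assume 45 completers, two-sided tests (the article does not state sidedness), a common residual variance, effects scaled to 95% omnibus power, and the assumed positions of conventional between sham and optimized. The critical values depend only on the number of sessions and the degrees of freedom.

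**What to change.** - In section 2.7, name two primary within-patient contrasts of the pre-to-post change in MEP amplitude at the hand-knob: optimized minus conventional, and optimized minus sham. Test each two-sided at 5%.
- State that the hypothesis is supported only if both are significant in favour of optimized.
- Keep the ANOVA, if wanted, as a supporting test, and state that its significance alone does not count as success.
- In the non-normal branch, name the same two contrasts as paired comparisons. The rank-sum test now listed is for independent samples, whereas every participant receives all three sessions.
- Report conventional minus sham descriptively, with its confidence interval.

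The cost is analysis wording only, with no new data or participants. Section 2.9 reports recruitment as still under way at publication; the change should be dated and made before unblinding. The price is that conventional versus sham loses confirmatory status, and neither named contrast can be claimed alone without a multiplicity adjustment. If separate claims are wanted, that adjustment should be specified now.

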#### Sample size

2.3.3

G*Power 3.1.9.7 (Franz Faul, Kiel, Germany) was used to determine the sample size. It was calculated based on the effect size determined by Lee et al. in 2015 for the pre-and post-tDCS intervention and MEP amplitude results (Lee et al., 2015). It was calculated using analysis of variance (ANOVA): repeated measures, within-between interaction, with a Type I error rate of 5% and a power of 95%, and with an effect size f of 0.2193764. Consequently, a sample size of 45 participants was required to determine the effectiveness of the intervention. A dropout rate of 10% was considered. Accordingly, 50 participants will be recruited for this study.

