## Discussion

3

The present crossover randomized control trial aims to determine the effect of personalized tDCS electrode positioning on the activation of the cortical region responsible for finger movement in patients with sub-acute or chronic stroke. The study design utilizes MEP data and 3D brain models derived from individual MRI scans to determine optimized tDCS electrode locations and compares them with conventional 10–20 EEG system electrode locations.

In general, anodal tDCS with low-intensity stimulation increases corticospinal excitability, whereas cathode stimulation may decrease it (Reed and Cohen Kadosh, 2018). However, tDCS has considerable inter-patient variability and a partially non-linear dose-dependent effect, as factors such as stimulation intensity and duration can diminish or reverse these effects (Laakso et al., 2015; Hassanzahraee et al., 2020). In patients with stroke, anode tDCS is frequently applied over the ipsilesional hemisphere, according to the interhemispheric competition model (Van Hoornweder et al., 2021). In this model, the underactive affected hemisphere experiences an inhibitory influence from the overactive unaffected hemisphere after a stroke (Di Pino et al., 2014). Consequently, the ipsilesional hemisphere is not only disabled due to stroke-induced tissue damage but also due to extensive interhemispheric inhibition (Van Hoornweder et al., 2021). Following this model, anodal tDCS increases cortical excitability by applying anode over the ipsilesional region and decreases contralesional cortical excitability through cathodal stimulation or through a bihemispheric electrode montage.

A study focused on the effect of tDCS on upper extremity function in patients with acute, sub-acute, or chronic stroke indicated that tDCS significantly improves upper limb function in patients with chronic stroke. In particular, bihemispheric tDCS seemed to have a fairly large effect on motor recovery of the upper extremity (Van Hoornweder et al., 2021). Although tDCS has been shown to be a promising tool to improve motor recovery after stroke, it is not yet widely used in clinical practice because of inconsistent effects reported in various meta-analyses (Van Hoornweder et al., 2021; Bornheim et al., 2022; van der Cruijsen et al., 2022). Currently, conventional tDCS results show variable E-fields within the motor cortex in patients with chronic stroke (Laakso et al., 2015).

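### Tukey's test after repeated measures ANOVA ordinarily puts one pooled error on all three session contrasts; the protocol's own rationale makes the required sphericity doubtful, and the plan has no safeguard for it

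*Protocol article*

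**What the plan says.** Section 2.7 (Statistical analyses) sets a Shapiro–Wilk check. For data that pass it, the main analysis is described in these words: "a repeated measures ANOVA test will be used for within-and in-between groups analysis". The follow-up comparisons between sessions then rest on one named procedure: "Tukey’s test will be used for" them. Results are to be shown with SDs, SEs and confidence intervals, "with the statistical significance threshold set at" p < 0.05. A rank-based route is named if normality fails. The section names no check, correction or alternative for unequal variances of the session differences, and it does not state the error term for the Tukey comparisons.

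Each participant receives all three sessions (2.1 Trial design), with motor-evoked potentials (MEPs) measured before and after each (2.6.1). The Abstract and Discussion state the hypothesis as optimized being greater than both conventional and sham, so optimized versus conventional is one of the two contrasts that matter.

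Three statements bear on the variances:

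- The Discussion says that "tDCS has considerable inter-patient variability and a partially non-linear dose-dependent effect".
- Section 2.4.1 describes a sham of 30-second ramps up to 1 mA and back down, at the start and again after 18 minutes.
- The Introduction expects individual modelling to make tDCS effects less variable.

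**The concern.** The classical Tukey procedure after a repeated measures ANOVA takes one mean square error and uses it for every pair. Each pair then has a correct SE only if all three within-patient differences have the same variance.

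The trial's rationale points the other way. If patients respond very differently to real current and sham delivers almost none, the active-minus-sham differences carry response variation that sham alone does not. The two active montages act on the same brain, lesion and target, so part of that variation may cancel in optimized minus conventional. If optimization also makes responses more uniform, the two active sessions differ in variance from each other. Equality of all three variances would then be a coincidence.

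At stake are the SE, interval and power of the individual contrasts, above all optimized versus conventional. The plan protects against non-normality but not against this.

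**Working it through.** **The plan's own figure.** Section 2.3.3 uses "repeated measures, within-between interaction", "with an effect size f of 0.2193764", alpha 5% and power 95%, and concludes that "a sample size of 45 participants was required to determine the effectiveness of the intervention". The article does not give the number of groups k, the number of measurements m, the correlation or the sphericity parameter. Taking k = 3, m = 6, correlation 0.5 and epsilon = 1:

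- λ = f²·N·m/(1 − 0.5) = 0.2193764² × 45 × 6/0.5 = 25.99
- df = (k−1)(m−1) = 10 and (N−k)(m−1) = 210
- power = 0.9545. At N = 42, λ = 24.26, df = 10 and 195, and power = 0.937.

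So 45 reproduces, and 45/0.9 = 50. The settings that reproduce it also assume sphericity (epsilon = 1).

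**Model for the contrasts (assumed).** There are 45 completers and three change scores each. Residual variance is 1 per session. Response SDs are tO (optimized), tC (conventional) and 0 (sham), with correlation r between a patient's two active responses. Period effects are left out. The documents give none of tO, tC or r, so ranges are shown.

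- Var(optimized − conventional) = 2 + tO² + tC² − 2·r·tO·tC
- Var(optimized − sham) = 2 + tO²
- Var(conventional − sham) = 2 + tC²
- Pooled value = mean of the three
- SE ratio for a pair = √(pooled / that pair's variance). Above 1 means the pooled SE is too wide.

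Example, tO = tC = 2, r = 0.8: the variances are 3.6, 6 and 6, and the pooled value is 15.6/3 = 5.2. The ratio for optimized versus conventional is √(5.2/3.6) = 1.20, and for each active versus sham √(5.2/6) = 0.93.

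| tO, tC, r | Opt–conv | Opt–sham | Conv–sham |
|---|---|---|---|
| 0.5, 0.5, 0.8 | 1.02 | 0.99 | 0.99 |
| 1, 1, 0.3 | 0.96 | 1.02 | 1.02 |
| 1, 1, 0.8 | 1.08 | 0.97 | 0.97 |
| 2, 2, 0.3 | 0.93 | 1.04 | 1.04 |
| 2, 2, 0.8 | 1.20 | 0.93 | 0.93 |
| 2, 2, 0.95 | 1.41 | 0.89 | 0.89 |
| 1, 2, 0.8 | 1.06 | 1.19 | 0.84 |
| 0.5, 2, 0.8 | 0.96 | 1.38 | 0.85 |

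**Where the pooled error is exact.** Setting the pooled value equal to Var(optimized − conventional) gives r = (tO² + tC²)/(4·tO·tC). This is 0.5 for equal SDs and 5/8 = 0.625 for SDs of 1 and 2. For SDs of 0.5 and 2 it is 4.25/4 = 1.06, which no correlation reaches, so there the pooled SE is always too narrow for this contrast. At r = 0.3 with those SDs the variances are 5.65, 2.25 and 6, the pooled value is 4.63, and the ratio is √(4.63/5.65) = 0.91.

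**Error rates and power (simulation, 40,000 runs per setting).** The pooled Tukey critical t is 2.384 (3 means, 88 df), a nominal per-pair rate of 1.9%. With each pair's own error it is 2.425 (44 df). The true effect is set to give 80% power with the correct SE on 88 df.

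| tO, tC, r | Per-pair error, opt–conv, pooled | Power, opt–conv: own error | Power, opt–conv: pooled |
|---|---|---|---|
| 0, 0 (sphericity holds) | 1.9% | 78% | 80% |
| 0.5, 0.5, 0.8 | 1.7% | 78% | 78% |
| 1, 1, 0.8 | 1.3% | 79% | 74% |
| 2, 2, 0.8 | 0.6% | 79% | 65% |
| 2, 2, 0.95 | 0.1% | 79% | 45% |
| 2, 2, 0.3 | 3.0% | 79% | 85% |
| 1, 2, 0.8 | 1.4% | 78% | 75% |

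The higher pooled power at r = 0.3 is bought with a per-pair error above nominal. With each pair's own error, the per-pair rate was 1.8% to 2.1% in every setting. Family-wise error of pooled Tukey was 4.8% to 6.0%.

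**The case against.** **The error term is not written down.** Section 2.7 names Tukey's test only, a studentized-range adjustment can be put on pair-specific SEs, and an analysis plan that is not shown may do so. This stands as a limit: a reader might infer that the protocol fixes a pooled error, and it does not say so. But the named pair of methods has an ordinary meaning, which is the pooled one, and the article does set out a fallback for the other main assumption. The point concerns a named method that fits the design poorly.

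**The premise is inferred.** A reader might conclude that only the active sessions carry individual response variation. No passage says that. The Discussion speaks of variability of tDCS in general, and section 2.4.1 describes the sham current, not the variance of MEP change after it. This makes equal variances doubtful. It does not prove them unequal.

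**Direction and size are open.** A reader might infer that the pooled error is simply wrong, that it always costs power for optimized versus conventional, or that it is right only at a correlation of 0.5. None of these holds. The last needs equal response variances in both active sessions, which the Introduction's expectation of less variable effects argues against. With response SDs of 1 and 2 at r = 0.8, the SE is only 6% too wide; with 0.5 and 2 it is 4% too narrow. The fall in power to 45% needs a response variance four times the residual and r = 0.95, neither of which is in the documents.

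**The model may not be the one planned.** Sections 2.3.3 and 2.7 speak of within-between terms, so the 88 df and the ratios belong to a three-change-score analysis assumed here. This stands too, and is a further reason to state the error term.

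**Conclusion.** The concern holds in a limited form. Tukey's test after a repeated measures ANOVA, in its ordinary form, rests on sphericity. The protocol's rationale makes that assumption doubtful, and the plan provides nothing if it fails.

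The size is conditional. For equal response SDs of 0.5 to 2 residual SDs and correlations of 0.3 to 0.95, the SE for optimized versus conventional lies between about 7% too narrow and 41% too wide; SDs of 0.5 and 2 at r = 0.3 extend the lower end to 9% too narrow. At SDs of 0.5 the error is 1% to 4% and can be ignored. Active-versus-sham SEs run from 16% too narrow to over 40% too wide once the active variances may differ.

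A reader might infer that the trial's overall false-positive rate is at risk. It is not to any serious degree: family-wise error stays at about 5 to 6%. The damage is to the individual contrast, whose interval, error rate and power may not be what they appear. This is a cheap improvement to make, not a defect that invalidates the analysis.

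**What to change.** State the error term, and make it specific to each contrast. Either estimate each of the three contrasts from its own within-patient differences with its own SD, or fit a mixed model with an unstructured covariance across the three sessions and Kenward-Roger degrees of freedom. Keep whatever multiplicity adjustment the sponsor chooses; Tukey's can be applied to these SEs. For the overall test, use the same covariance or a Greenhouse-Geisser correction.

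The cost is wording in the analysis plan, with no change to conduct or sample size. Error degrees of freedom per contrast fall from (45−1)×2 = 88 to 44, so the unadjusted two-sided 5% t value rises from 1.987 to 2.015. If sphericity holds after all, about 1 point of power is lost. Section 2.9 reports that recruitment is still under way, so the choice can be fixed before the data are analysed.
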